### Qualitative data collection

The qualitative data collection will be conducted between one and four months after quantitative data collection finishes, to minimise recall bias. Interviews will be digitally recorded and translated and transcribed by experienced local experts. Each transcription will be checked and validated by the researcher who conducted the interview.

### Data management and quality assurance

A researcher will be employed at each participating centre. This person will be responsible for managing recruitment, data collection and data entry. Fortnightly study team conference calls will be used to ensure that all queries are promptly resolved, attended by all members. All quantitative data will be double-entered into purpose designed EpiData databases. Discrepancies will be resolved by referring back to the original questionnaires.

Following data checking and cleaning, the data will be imported into Stata for analysis at KCL. Qualitative transcripts will be imported into NVivo (version 9) for analysis. All hard data will be stored for at least seven years in accordance with the UK Data Protection Act 1998.

### Analysis

#### Quantitative analysis

Data will be described in two stages:

1) Cross sectional baseline analysis: descriptive analysis of demographic and clinical variables, baseline primary and secondary outcomes for the two groups (standard care and palliative care). Continuous variables will be presented as mean (standard deviation), median (range); categorical variables will be described as proportions. Baseline scores for primary and secondary outcome variables for two groups will be compared using two-sample t-test (or Mann–Whitney U test if non-normal distribution) for continuous data and Chi square test for categorical data.

2) Summary measures: change in primary and secondary outcomes from baseline to the final time point will be summarized, using paired t-tests or the non-parametric equivalent.

Longitudinal analysis will be performed to address the primary study objectives of comparing pain and other symptoms, (objective 1) and subsequently adherence (objective 2), health related quality of life (objective 3) and multidimensional palliative care outcomes such as psychological and spiritual well-being (objective 4), in the intervention and control groups. Factors of the APCA African POS were identified from APCA POS data from similar samples (high prevalence of HIV) in Sub Saharan Africa [60]. Three factors were identified which covered 1) physical and psychological symptoms, 2) interpersonal dimension and 3) the existential dimension. They will be analysed for differences between intervention and control groups. For continuous outcomes, the change in scores for two groups will be compared using general linear model with adjustment of baseline differences and covariates (demographics and clinical variables). For categorical outcomes, the two-group comparisons will be implemented using generalized linear model and adjusting for design effects, the repeated measures will be taken into account using generalized estimating equations (GEE) technique.

The analysis will follow the principle of intention-to-treat. The p-values reported will be two-tailed and an alpha level of 0.05 will be used to assess statistical significance. The analysis will be carried out using non-missing data. The pattern of missing data and drop-outs will be investigated and sensitivity analysis will be performed to assess their impacts on outcomes. If the impact is great, a missing data strategy will be put in place using mean horizontal imputation and last value carried forward.

Further descriptive analysis will be conducted to determine the common features and differences between the three palliative care facilities, and the services received as recorded in the CSRI. Analysis of the CSRI will also allow us to determine a dosage effect for receipt of palliative care, as well as allow an evaluation of the palliative care received with respect to outcomes.

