### Minimum package of palliative care

Patients allocated to the intervention arm will receive an initial clinical assessment , followed by either one further visit or phone call within the first week, one further visit or phone call within the second week and one visit per month thereafter. The focus of the care provided will be on holistic assessment and management of physical, psychological, spiritual and social problems. This minimum package of care can be supplemented by additional clinical support as required on a case-by-case basis.

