### Compensation

Study participants are not given financial compensation for their time, but they are given $5USD towards transport expenses for data collection appointments. Transport for intervention patients clinical appointments (of which there are at least two more than research appointments) are not reimbursed as this may influence the outcome. For comfort, participants are given a drink and small snack on arrival for their data collection appointments.

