#### Client services receipt inventory (CSRI)

##### Administered at months 0, 1, 2, 3 and 4

The CSRI aims to explore the components of care received by patients. The version of the CSRI used in this study is based was adapted from versions used in other palliative care research and adapted for use in Africa [58,59]. The version used for this study has been simplified in that instead of documenting time, the researcher records whether the client has received a service or not as a binary outcome.

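### The protocol says the CSRI will establish a dosage effect of palliative care, but the CSRI records only yes/no receipt of services and care above the minimum follows need, so only a coarse, non-causal description is possible

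*Protocol article*

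**What the plan says.** The last paragraph of the protocol article's Quantitative analysis section plans a description of the facilities and of the services recorded in the CSRI, and then goes further: "Analysis of the CSRI will also allow us to determine a dosage effect for receipt of palliative care". The same sentence adds an evaluation of the palliative care received with respect to outcomes.

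The section on the Client services receipt inventory gives its purpose as "The CSRI aims to explore the components of care received by patients" and its timing as "Administered at months 0, 1, 2, 3 and 4". It also says that the instrument was simplified for this study: "instead of documenting time, the researcher records whether the client has received a service or not as a binary outcome".

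Under Minimum package of palliative care, each intervention patient has an initial assessment, a visit or call in week 1, then "one further visit or phone call within the second week and one visit per month thereafter". The section continues: "This minimum package of care can be supplemented by additional clinical support as required on a case-by-case basis". The Referral section opens the hospice to intervention patients whose problems are complex or appear refractory. The Compensation section says of the intervention clinical appointments, "of which there are at least two more than research appointments", that travel to them is not reimbursed.

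**The concern.** Two things do not fit the promise of a dosage effect.

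The first is measurement. A dosage effect needs a measure of amount. The instrument named for it has had time removed and carries no count of contacts. No later analysis plan can recover a count from a yes/no item.

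The second is design. Patients are randomised to palliative care or not, and not to different amounts of it. Within the intervention arm, care above the minimum is decided after randomisation in response to the patient's problems, which are also what the outcomes measure. The covariate adjustment in the Quantitative analysis section is described for the comparison of the randomised groups and does not address this.

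At stake is a secondary statement about whether more palliative care gives better outcomes. Such a statement is easily read as causal when it comes from a randomised trial, and here it could be empty or point the wrong way.

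**Working it through.** The document gives no figure for the dosage analysis, so there is none to reproduce. The check has three steps.

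**1. What the CSRI can record**

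- Scheduled contacts over four months (Minimum package): 1 initial + 1 in week 1 + 1 in week 2 + 3 or 4 monthly visits = 6 or 7.
- Cross-check (Compensation): five data collection points (months 0 to 4) plus at least two = at least 7.
- CSRI records after randomisation: months 1, 2, 3 and 4. The month 0 record precedes allocation. One service item therefore gives at most 4 yes answers.

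The initial assessment and the contacts in weeks 1 and 2 all fall before the month 1 interview, so three contacts of the same service type become one yes. In any later month, one contact and several look alike. What remains is a count of months with receipt (0 to 4 per service) and a count of service types used.

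**2. How much a month count could carry (illustration)**

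Assumptions, not from the document: each monthly visit is attended with probability 0.94; extra contacts are Poisson with mean 0.5 a month; a single item asks about any palliative contact.

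- Probability of a no in a month: 0.06 × e^(−0.5) = 0.0364. Probability of a yes: 0.9636.
- Share with yes in all four months: 0.9636^4 = 0.86.
- SD of the monthly item: √(0.0364 × 0.9636) = 0.187.
- Correlation of the month count with extra contacts: (0.5 × 0.0364) / (0.187 × √0.5) = 0.14.
- Correlation with contacts actually made (attended visits plus extras, mean 1.44 a month, variance 0.94 × 0.06 + 0.5 = 0.556): (1.44 × 0.0364) / (0.187 × √0.556) = 0.38.

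So the month count holds some information, mainly about missed visits, and little about additional care.

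**3. What need-driven care does to the slope (illustration)**

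Now suppose that contacts are counted exactly. Further assumptions: need has SD 1; month 4 pain rises by 1 unit per SD of need; the log rate of extra contacts changes by b per SD of need. Over four months the mean number of extra contacts is 2, so Cov(need, contacts) = 2b and Var(contacts) = 2 + 4(e^(b²) − 1). If contacts have no effect at all, the slope of pain on extra contacts is

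2b / [2 + 4(e^(b²) − 1)].

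| b | Slope when the true effect is 0 | Slope when the true effect is −0.20 |
|---|---|---|
| 0 | 0 | −0.20 |
| 0.3 | 0.6 / 2.377 = +0.25 | +0.05 |
| 0.6 | 1.2 / 3.733 = +0.32 | +0.12 |
| −0.3 | −0.6 / 2.377 = −0.25 | −0.45 |

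A simulation with 56 patients in the arm and 4,000 runs agreed for the non-negative values of b: +0.25 and +0.33 under no effect, +0.05 and +0.13 under a true −0.20. Adjusting for baseline pain (assumed correlation 0.5 with need) left +0.20 and +0.27 under no effect, and about 0 and +0.07 under a true −0.20. Where sicker patients receive more (b > 0), a real benefit is hidden or reversed. Where patients in less need attend more (b < 0), a benefit appears or is exaggerated.

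**The case against.** The other side has several good points.

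- **A coarse score exists.** The CSRI is taken at four follow-ups and covers components of care. Months with receipt and number of service types can be scored. With unpaid travel, missed visits are plausible, and a monthly yes/no record can show them. This stands: it would be wrong to infer that exposure cannot be measured at all.
- **The item list is not shown.** A reader might infer that the CSRI merely repeats the allocation, yes throughout one arm and no throughout the other. That treats the scheduled package as delivered and the inventory as one item, and the document supports neither.
- **The direction is open.** A reader might infer that the bias must run against the intervention. Extra care given for need suggests this, but unreimbursed travel could mean that better-off or more motivated patients attend more, which biases the other way.
- **Objective 5 does not depend on it.** A reader might infer that finding the most effective component rests on the CSRI. The Abstract, the Aim, the interview schedule and the qualitative analysis assign process and mechanism mainly to the qualitative component.
- **The paragraph is descriptive, and detail may sit elsewhere.** How exposure is scored or need adjusted for can be left to the full protocol or analysis plan. But the quoted sentence adds an effect claim to the descriptive one before it, and that claim conflicts with the instrument as described. This is a contradiction within the article and not an omission.

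**Conclusion.** The point holds as a contained one about a secondary claim. The CSRI as described supports at most a coarse exposure score and cannot distinguish patients by number or intensity of contacts within a month. Any association between amount of care and outcome is a non-randomised comparison open to confounding by need. Its size and direction cannot be derived from the document.

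The firm figures are the minimum of about 7 contacts against at most 4 follow-up yes answers per service. The 86%, the correlations of 0.14 and 0.38 and all slopes rest on assumed attendance, contact rates and strength of need. They show that the mechanism can matter and do not estimate the bias in this trial.

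The primary intention-to-treat comparison of pain is unaffected, and objective 5 rests mainly on the qualitative work. The wording should still be changed, because the planned analysis cannot deliver what the sentence promises.

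**What to change.** 1. Remove the dosage-effect wording from the CSRI sentence in Quantitative analysis.
2. Describe the CSRI analysis as an exploratory, non-causal account of services received by arm, and name the exposure summaries to be used, for example months with receipt and number of service types.
3. Where the number of contacts, calls or hospice referrals is of interest, take counts from the intervention nurses' clinical documentation to the extent that it records them. The article says that referral criteria are recorded there and that clinical-encounter documentation will be collected. It does not say that every call is logged.
4. Label any within-arm association between care received and outcome as descriptive, and state the possibility of confounding by need beside it.

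A complier average causal effect of the full minimum package, with allocated arm as instrument, is not recommended as a replacement. It requires allocation to act only through completing the package, and patients who receive part of it may also benefit.

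The cost is the wording change, some extra data entry and a more modest secondary claim. Recruitment, follow-up and the primary analysis do not change.

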#### Qualitative analysis

Analysis of translated transcripts will be conducted using thematic content analysis [61]. The coding frame will be developed initially deductively, using themes from the topic guide, combined with inductive themes which emerge from the data, which will be generated iteratively as the analysis progresses. The coding will be conducted separately by two researchers, one from the study site and one from the UK, and then merged, to ensure a comprehensive and culturally sensitive framework.

The preliminary findings will be cross checked by the researcher based at the study site and presented to the study team in each country for proxy member checking to improve validity [62].

A model of the mechanism of the psychosocial aspect of palliative care will be constructed on the basis of the data if possible and relevant.

### Dissemination

The audience for dissemination will include collaborating centres, participants, HIV clinicians, academic teaching staff in Africa, local community groups and non-governmental organisations, academic global research audiences, Ministries of Health and international non-governmental organisations.

## Discussion

The data provided by this study will provide evidence to inform the provision of palliative care for people living with HIV and on ART, building on our previous work describing the palliative care problems of this group [8,10,24,46].

Aspects of this study are unique and will contribute to the body of knowledge. The choice of study design, the first RCT in this field, will provide a clear answer to the question of whether palliative care for this group is effective and relevant. The multi-country aspect will illuminate the differences between low and middle income countries, and Southern and Eastern Africa, without inviting direct comparison of outcomes of two very different countries. Researchers in both countries will be locally recruited and trained by staff from King’s College London, building local capacity. Steps have been taken to reduce potential bias, including using locally validated tools, which have been translated in all three study languages by experienced translators. Researchers have been trained on aspects of data collection, bias minimisation and potential sources of contamination and data will be double entered to avoid inaccuracies from human error.

The publication of this protocol presents increased transparency in the aims and objectives of the study and analysis of the generated data.

## Abbreviations

APCA: African palliative care association; ART: Anti retroviral therapy; CSRI: Client services receipt inventory; ECOG: Eastern co-operative global performance scale; GHQ: General health questionnaire; HIV: Human immunodeficiency virus; HPCA: Hospice and palliative care association; KEHPCA: Kenyan hospice and palliative care association; MOS-HIV: Medical outcomes study HIV; MRC: Medical research council; PEP: Post exposure prophylaxis; PMTCT: Prevention of mother to child transmission; POS: Palliative outcomes scale; RCT: Randomised controlled trial; TB: Tuberculosis; WHO: World health organisation.
